### Intervention

The intervention consists of 3 MMS messages with nutritional information per week for 12 consecutive weeks. The messages were reviewed by a perinatal psychologist. The messages will be sent as follows: Monday at 3 PM, the message that addresses the cognitive domain will be sent; Tuesday at 3 PM, the message that addresses the affective domain will be sent; and Thursday at 3 PM, messages that address the psychomotor domain, together with the weekly user satisfaction survey, will be sent. This delivery scheme was validated in the pilot study that was carried out. The 12 topics related to nutrition during pregnancy will be addressed, 1 will be addressed per week, and 3 messages will be sent for each topic. At the beginning of each month, messages will be sent to pregnant women who were recruited during the immediately previous month. In the development of the project and to prevent pregnant women from incurring additional expenses for participating in the intervention, we will directly recharge the phones of the users who participate in the study.

### Follow-up

The team of midwives will keep a record of the weight of the pregnant women who attend their prenatal checkups monthly. Therefore, the monitoring of the weight of both groups will be done through the midwives in order not to request sensitive data via MMS.

### Dropouts

A record of the number of pregnant women who drop out of the study will be kept, as well as their characteristics for subsequent statistical analysis.

### Primary and Secondary Outcomes

The primary outcome will be to assess the effectiveness of the mHealth mami-educ intervention in reducing the incidence of eGWG compared to routine care. Secondary outcomes will include identifying the barriers and facilitators influencing weight gain in pregnant women to compare the maternal outcome of pregnancy, in terms of complications developed during pregnancy (pre-eclampsia, gestational diabetes, and gestational hypertension), and the perinatal outcomes (prematurity and birth weight) of the pregnant women in the control and intervention groups.

### Statistical Analysis

The data analysis plan will be governed by the intention-to-treat principle, as we will include all participants who were randomly assigned after recruitment, assuming that participants who drop out are treatment failures. The effectiveness of the treatment will be measured using the chi-square test (χ^2^), comparing the intervention group with the control group in terms of the percentage of women who are classified as having excessive weight gain at the end of pregnancy. To confirm the effectiveness of the intervention, a significant decrease (*P*<.001) of women with eGWG in the intervened group will be expected. For data analysis, the statistical software GraphPad Instat 3.0b and GraphPad Prism 6.0f (GraphPad Software Inc) will be used. *P*<.001 (determined by a 2-sided test) will be considered statistically significant.

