### Sample Size Calculation

The total sample consists of 511 participants, which will be divided into 2 groups. In the El Bosque CESFAM, 280 pregnant women were recruited, with an estimated dropout rate of 30% (based on the pilot study carried out) to guarantee the required sample size of 210 pregnant women with a confidence level of 90% and a 5% error. At Segismundo Iturra CESFAM, 231 pregnant women were recruited, with the same estimated dropout rate, to ensure a sample size of 178 pregnant women with a confidence level of 90% and a 5% error. For the calculation of the sample size, the official records of the DEIS regarding the number of pregnant women between 20 and 44 years of age who were treated for prenatal control in the CESFAM of the El Bosque commune and Segismundo Iturra were considered. The recruitment period will be 6 months.

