### Limitations

A limitation of this study is the reliance on smartphones to access interventions. In addition, the recruitment of pregnant women must occur during the first trimester of gestation, and this may be hindered because some pregnant women begin prenatal care in the second trimester. Another limitation is that the pregnant woman may decide not to interact with the messages by blocking the number of the intervention.

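### Scoring every dropout as excessive weight gain in the primary test, with 30% dropout expected and dropout undefined, dilutes a real effect and biases the contrast if dropout differs between arms

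*Protocol article*

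**What the plan says.** Statistical Analysis describes an intention-to-treat analysis that includes all randomised women, "assuming that participants who drop out are treatment failures". The primary comparison is a chi-square test on the percentage of women classified as having excessive weight gain at the end of pregnancy, with significance set at two-sided P<.001.

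Sample Size Calculation states that "The total sample consists of 511 participants, which will be divided into 2 groups". For the El Bosque centres it says "280 pregnant women were recruited, with an estimated dropout rate of 30" per cent, based on the pilot, and it applies the same rate at Segismundo Iturra.

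Follow-up says that "the monitoring of the weight of both groups will be done through the midwives", outside the messaging system, for women who attend prenatal checkups. Dropouts says that the number and characteristics of women who drop out of the study will be recorded. No section defines dropout or says what happens to weights recorded for a woman who drops out.

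Procedures ends the study when the intervention participants have completed the 12-week message period.

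**The concern.** The failure rule assigns an outcome to a dropout instead of measuring it. If dropout runs as expected, nearly a third of the primary outcomes would be set to eGWG by convention. The test then compares a mixture of two things: the difference in eGWG among women who stay and the difference in dropout between arms. When dropout is equal, the mixture weakens a real effect. When it is unequal, the dropout difference enters the result as if it were a treatment effect, in either direction.

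The plan also has a weight source that does not depend on the messages, so at least some of the outcomes that the rule would assign could be measured. The rule is written into the protocol, so an analysis plan that follows it will carry it forward.

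**Working it through.** **The plan's own figure.** 280 + 231 = 511, as stated. The required numbers are 210 and 178. Inflating for 30% dropout gives 210/0.70 = 300 and 178/0.70 = 254.3, rounded up to 255, a total of 555. The recruited numbers less 30% leave 280 × 0.70 = 196 and 231 × 0.70 = 161.7, below 210 and 178. The 511 therefore does not follow from a 30% allowance. That is a separate matter; 511 is used below as the planned total.

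**Inputs.** From the protocol: total 511, so n = 255.5 per arm (the even/odd assignment implies about 1:1); dropout d = 0.30; two-sided alpha 0.001, so z = 3.2905. Assumed, because the protocol gives neither: the eGWG rates and the dropout in each arm.

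**Scored rate under the rule.** For true rate p and dropout d, the scored rate is p′ = d + (1 − d)p. With equal d, and dropouts otherwise like completers, the scored difference is (1 − d) times the true difference, which is 0.70 times at d = 0.30.

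- 50% vs 35%: 0.30 + 0.70 × 0.50 = 0.650 and 0.30 + 0.70 × 0.35 = 0.545. A 15-point effect becomes 10.5 points, and the risk ratio moves from 0.70 to 0.84.
- 50% vs 40%: 0.650 and 0.30 + 0.70 × 0.40 = 0.580. A 10-point effect becomes 7 points.

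**Power.** Φ[(Δ − z × SE0)/SE1], with SE0 the pooled and SE1 the unpooled standard error of the difference.

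- 50% vs 35%, weights for all: SE0 = 0.04374, SE1 = 0.04323; (0.15 − 3.2905 × 0.04374)/0.04323 = 0.141; power 56%.
- The same effect under the rule: SE0 = 0.04339, SE1 = 0.04314; (0.105 − 3.2905 × 0.04339)/0.04314 = −0.876; power 19%.
- The same effect, observed 70% only (0.70 × 255.5 = 178.85 per arm): SE0 = 0.05228, SE1 = 0.05167; (0.15 − 3.2905 × 0.05228)/0.05167 = −0.426; power 34%.

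| Assumed eGWG, control vs intervention | Weights for all | Observed 70% only | Dropout = failure |
|---|---|---|---|
| 50% vs 35% | 56% | 34% | 19% |
| 50% vs 40% | 15% | 8% | 5% |

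Over assumed control rates of 30% to 60% and reductions of 10 to 20 points, power is 4% to 51% under the rule and 15% to 99% with weights for all.

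**More dropout in the intervention arm (35% vs 25%), true 50% vs 40%.** Control: 0.25 + 0.75 × 0.50 = 0.625. Intervention: 0.35 + 0.65 × 0.40 = 0.610. A true 10-point benefit appears as 1.5 points.

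**More dropout in the control arm (35% vs 25%), no true effect.** The spurious benefit is (0.35 − 0.25)(1 − p) = 0.10(1 − p). The chance of a significant result in favour of the intervention uses the same formula; its nominal value is 0.05%.

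| Assumed eGWG in both arms | Scored control vs intervention | Spurious benefit | False rejection in that direction |
|---|---|---|---|
| 30% | 54.5% vs 47.5% | 7 points | 4.3% |
| 40% | 61.0% vs 55.0% | 6 points | 2.7% |
| 50% | 67.5% vs 62.5% | 5 points | 1.7% |
| 60% | 74.0% vs 70.0% | 4 points | 1.1% |

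**Availability of late weights.** A woman enrolled at 12 weeks may wait up to about a month (roughly 4 weeks) for messages to begin and then receives them for 12 weeks: 12 + 4 + 12 = about 28 weeks. For the last women recruited, the stated end of study would come well before the end of pregnancy.

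**The case against.** The best defence is that failure scoring is a familiar conservative convention, that dropouts will be recorded and described, and that sensitivity analyses and imputation belong in an analysis plan that is not shown. The last part is fair as far as omissions go, but the primary rule itself is stated here. The convention is conservative for a claim of benefit only when dropout is equal or higher in the intervention arm, and even then it costs power.

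Several stronger readings are tempting, and the protocol does not support them:

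- **Blocking messages counts as dropout, so dropout must be higher in the intervention arm.** Limitations says that "the pregnant woman may decide not to interact with the messages by blocking the number of the intervention", but presents this as a limitation, not as dropout. If it did count, the bias would run against the intervention. The documents give no specific reason to expect more dropout among controls, so false benefit is a possibility, not a prediction.
- **Most dropouts will have a usable weight, so the rule is unnecessary.** Follow-up covers women who attend checkups. Weights do not depend on messaging, but they do depend on attendance. How many of the expected 30% would have a late weight is unknown.
- **False positives are common.** At a conventional 0.05 the inflation would look large (17% to 35% in the control-arm scenario above), but the protocol tests at 0.001, where it is 1.1% to 4.3%. That is small in absolute terms, though many times nominal.
- **The rule also corrupts birth weight and complications.** The failure wording leads straight into the eGWG test, and the Abstract assigns maternal and perinatal outcomes to logistic regression. Nothing codes those outcomes as failures.

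It is also true that power at 0.001 is poor for modest effects even without the rule. And if women who disengage gain no benefit, their observed weights will dilute the effect too; that dilution is part of the intention-to-treat effect, whereas the rule's is an artefact of scoring.

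**Conclusion.** The concern holds for the primary eGWG analysis. The mechanism follows from the stated rule and needs no assumption about eGWG rates: equal 30% dropout multiplies the risk difference by 0.70 when dropouts are otherwise like completers, and unequal dropout shifts the contrast towards whichever arm loses fewer women.

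The sizes are illustrative, because the protocol gives neither eGWG rates nor dropout by arm. In both examples worked through, the rule has lower power than simply analysing the observed 70%. The figures for weights on all women are an upper bound: they require a late weight for everyone and the same effect in dropouts as in completers. The false-benefit figures require control dropout to exceed intervention dropout by 10 points. What the documents support is a primary estimate open to distortion in either direction, not a forecast that the trial will falsely show benefit.

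**What to change.** Replace the failure rule in Statistical Analysis along these lines:

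- Define dropout, separating stopping the messages from leaving care and from withdrawing from the study.
- In the primary analysis, determine eGWG from midwife-recorded weights for every randomised woman who has a usable late weight, whether or not she engages with the messages.
- Handle truly missing weights by a prespecified method, for example multiple imputation using arm, BMI stratum, site and earlier recorded weights.
- Keep dropout = failure as a sensitivity analysis for eGWG only, and report dropout by arm.
- Reconcile Procedures, where the study ends with the message period, with Statistical Analysis, where the outcome is at the end of pregnancy, so that late weights are collected for both arms.

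The cost is revised wording, modest extra programming, and follow-up to the end of pregnancy if it is not already intended. Imputation of this kind also relies on a missing-at-random assumption for women without a late weight, which the retained sensitivity analysis helps to probe.

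### The stated required sample size has no link to the two-arm chi-square at P<.001 that decides effectiveness, and gives that test low power for 10- to 15-point reductions

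*Protocol article*

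**What the plan says.** **Sample size (Protocol article, Sample Size Calculation).** "The total sample consists of 511 participants, which will be divided into 2 groups". The El Bosque figure is set "to guarantee the required sample size of 210 pregnant women with a confidence level of 90% and a 5% error", and the Segismundo Iturra figure "to ensure a sample size of 178 pregnant women with a confidence level of 90% and a 5% error". The stated source is "the official records of the DEIS regarding the number of pregnant women between 20 and 44 years of age" seen for prenatal care at each site. Expected dropout is 30%. The section gives no control rate of excessive gestational weight gain (eGWG), no target difference and no power.

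**Test (Protocol article, Statistical Analysis).** The two arms are compared by chi-square on the percentage of women with eGWG at the end of pregnancy. Everyone randomised is analysed, and dropouts count as treatment failures. To confirm effectiveness, a decrease significant at .001 "of women with eGWG in the intervened group will be expected". The section closes with the general rule that "P*<.001 (determined by a 2-sided test) will be considered statistically significant".

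**Outcomes (Primary and Secondary Outcomes).** One primary outcome is named: effectiveness in reducing the incidence of eGWG compared with routine care.

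**The concern.** A confidence level, an error and a population count, applied separately to each site, are the inputs for estimating one proportion in one finite population. The size of a randomised comparison depends on two event rates, an alpha and a power. It does not depend on how many women attend a clinic. The word *required* in the sizing section therefore has no basis in the test that decides the trial.

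The threshold of .001 matches neither the 90% nor the 5% in the sizing section. With a single primary outcome, multiplicity does not explain it, and no other reason is given.

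At stake is the primary conclusion. The article's Conclusions say that the data will determine whether the programme reduces excessive weight gain. If power is low for plausible reductions, a real benefit is likely to be reported as unconfirmed.

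**Working it through.** **1. Where 210 and 178 may come from.** The population counts are not given, so the figures cannot be fully reproduced. Assume a one-proportion precision formula with finite population correction and p = 0.5:

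- n0 = z² × 0.25 / 0.05² = 1.645² × 0.25 / 0.0025 ≈ 270.6
- n = N × n0 / (N − 1 + n0)

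This returns 210 at N of about 935 and 178 at N of about 518. That is compatible with the stated figures, but it does not prove the formula: N is free, so almost any n below 271 can be matched.

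**2. Inputs for the test.**

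- From the document: two-sided alpha 0.001; allocation of about 1:1 (even and odd random numbers); 210 + 178 = 388 women (194 per arm) or 511 (255.5 per arm); 30% dropout; dropouts counted as failures.
- Assumed: control eGWG of 40-50%; reductions of 10, 15 and 20 points; equal dropout in both arms; a failure counted as eGWG.

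**3. Power formula (pooled variance under the null).**

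Power = Φ[(d − z × SE0) / SE1], where SE0 = √(2p̄(1 − p̄)/n), SE1 = √((p1(1 − p1) + p2(1 − p2))/n), and z = 3.291 at .001 or 1.960 at .05.

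Example, 50% vs 40% with 194 per arm at .001: SE0 = 0.0505 and SE1 = 0.0503, so (0.10 − 3.291 × 0.0505)/0.0503 ≈ −1.32 and power is about 9%.

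**4. Dropouts as failures.** With 30% dropout in each arm, a completer rate p becomes 0.3 + 0.7p. So 50% vs 40% becomes 65% vs 58%, and a 10-point difference shrinks to 7 points. With 255.5 per arm, SE0 = 0.0431 and SE1 = 0.0429, so (0.07 − 3.291 × 0.0431)/0.0429 ≈ −1.67 and power is about 5%.

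**5. Results (control eGWG 40-50% among completers).**

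| Analysis set | Reduction | Power at .001 | Power at .05 |
|---|---|---|---|
| 388, no dilution | 10 points | 9-11% | 51-54% |
| 388, no dilution | 15 points | 38-45% | 85-89% |
| 511, no dilution | 10 points | 15-18% | 62-66% |
| 511, no dilution | 15 points | 56-63% | 93-95% |
| 511, no dilution | 20 points | 91-95% | over 99% |
| 511, 30% dropouts as failures | 10 points | 4-5% | 36-37% |
| 511, 30% dropouts as failures | 15 points | 18-19% | 66-68% |
| 511, 30% dropouts as failures | 20 points | 45-47% | 89-90% |

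**6. Difference detectable with 80% power.**

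- 388 women, no dilution: 19-20 points at .001 and 13-14 at .05. Widening the control rate to 30-60% gives 17-21 and 12-14.
- 511 randomised, 30% dropouts as failures: about 26 points among completers at .001 and about 17-18 at .05.

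**7. Evaluable women.** 511 × 0.7 ≈ 358, so 388 is not what remains after the stated dropout.

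**The case against.** **The survey formula is an inference.** This stands. A reader might take the match at N of 935 and 518 as proof, but the article gives no counts and names no formula. The point does not depend on it. If the wording was meant as 90% power and 5% alpha, 0.05 still disagrees with the .001 decision rule, and no effect size is stated.

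**A strict alpha is conservative, not wrong in itself.** This also stands. The defect is that the size was never tied to the threshold. A reader might also call .001 a hundred times stricter than the 10% implied by 90% confidence, but that sets an interval's confidence level against a test's alpha and is not a valid comparison.

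**The power loss can be overstated.** A reader might infer that any useful benefit would almost certainly be missed. The document does not say what reduction is useful. With all 511 analysed and no dilution, power at .001 is 56-63% for 15 points and 91-95% for 20. The low figures hold for 10 points, for 388 women, and under the dropout rule.

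**A fuller protocol or SAP may hold a power calculation.** Possibly. But this is not an omission: the article itself states both a basis for its required size and a decision threshold, and the two do not fit together.

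**Conclusion.** The point holds. The sizing and decision rules use unrelated criteria, and the size called required is not shown to support the stated test.

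Power at .001 under the plan's own analysis rule is about 4-5% for a 10-point reduction and 18-19% for 15 points. Without dropout dilution it ranges from 9% to 18% for 10 points and from 38% to 63% for 15 points, depending on whether 388 or 511 women are counted. The size would be adequate only for a reduction of about 20 points with all 511 analysed and undiluted, and the article neither states nor justifies an effect that large.

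These figures rest on an assumed control rate of 40-50%, 1:1 allocation and, for the dropout rule, 30% loss in each arm with every loss counted as eGWG. The mismatch itself rests on the text alone.

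A reader might also infer that moving to 0.05 lets the trial claim 80% power for 13-14 points. That holds only for 388 evaluable women without dropout dilution, which is not the analysis described.

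**What to change.** 1. In Statistical Analysis, set the single primary test at two-sided 0.05, report the risk difference with its 95% CI, and remove the .001 rule. Data collection began in May 2022 and 76 women had joined by the end of November 2022, so this needs a dated, justified amendment made before any between-arm outcome data are examined. A later relaxation would look data-driven.

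2. In Sample Size Calculation, replace the survey-style justification with the two-arm difference that the trial can detect. State the assumed control rate, power and alpha (the same alpha as the test). Compute it for the attainable number and under the dropout-as-failure rule. For 511 randomised with 30% dropout and 40-50% control eGWG, the statement would be roughly 17-18 points among completers for 80% power at 0.05. Rerun it if fewer are recruited.

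**Cost.** Two revised paragraphs, a documented mid-trial amendment and no extra participants. The price is a conventional 5% type I error in place of 0.1%, and a less favourable sample-size statement.

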**Methods:**

The design of the intervention corresponds to a classic randomized clinical trial. The participants are pregnant women in the first trimester of pregnancy who live in urban and semiurban areas. Before starting the intervention, a survey will be applied to identify the barriers and facilitators perceived by pregnant women to adopt healthy eating behaviors. The dietary intake will be estimated in the same way. The intervention will last for 12 weeks and consists of sending messages through a multimedia messaging service with food education, addressing the 3 domains of learning (cognitive, affective, and psychomotor). Descriptive statistics will be used to analyze the demographic, socioeconomic, and obstetric characteristics of the respondents. The analysis strategy follows the intention-to-treat principle. Logistic regression analysis will be used to compare the intervention with routine care on maternal pregnancy outcome and perinatal outcome.

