eGWG during early pregnancy has been repeatedly associated with increased adiposity in childhood and adolescence [11-15]. Thus, adequate maternal nutrition during pregnancy is the window of opportunity to strengthen the health status of the mother and fetus and reduce the risk of adverse birth outcomes, such as preterm birth and low birth weight associated with eGWG [16]. The first trimester of pregnancy is critical for short-term interventions to break the “transmission” of obesity from one generation to the next [17]. For many women, pregnancy is a powerful motivator for self-care, as they are more aware of personal risks and have a strong emotional response toward adopting risk-reducing behaviors [18]. Quantitative literature suggests that the key to maintaining a healthy pregnancy and the primary prevention of maternal-fetal complications is establishing healthy dietary behaviors during gestation [19,20]. Even though many women are aware of the importance of healthy eating during pregnancy, the lack of nutritional self-care knowledge represents a substantial barrier to weight control during this stage [21,22]. Nutrition education improves nutritional knowledge, thus influencing practices aimed at achieving adequate nutrition [22]. Several studies recommend the continuous use of educational interventions on nutrition during pregnancy in routine obstetric practice to improve the quality of life of pregnant women and their offspring [6,23-25]. Regarding this, a study performed on the Chilean population evaluated the efficacy of a low-intensity, high-coverage nutritional intervention at the primary health care level [26]. This high-coverage intervention included training health professionals on nutritional recommendations, counseling pregnant women on diet and physical activity, and appropriate referral to primary health care centers’ dieticians. The study found that the intervention reduced gestational weight gain and has the potential for successful scale-up [26].

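### The closing P<.001 rule is not limited to the primary outcome, so read literally it also governs the binary complication and prematurity comparisons, where a true doubling of a 5% to 10% risk would usually be called not significant

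*Protocol article*

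**What the plan says.** The Statistical Analysis section of the protocol article uses P<.001 twice. The first use concerns the primary outcome: to confirm effectiveness, a decrease at that level "of women with eGWG in the intervened group will be expected". The second is the last sentence of the section. It names no outcome and makes P<.001 the general standard: that level "determined by a 2-sided test) will be considered statistically significant". No other threshold is stated in the article, and no reason is given for this one.

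The Primary and Secondary Outcomes section lists, as secondary comparisons between the arms, "complications developed during pregnancy (pre-eclampsia, gestational diabetes, and gestational hypertension), and the perinatal outcomes (prematurity and birth weight". The abstract's Methods paragraph says how they are analysed: "Logistic regression analysis will be used to compare the intervention with routine care on maternal pregnancy outcome and perinatal outcome". No threshold is given there.

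**The concern.** A very strict threshold protects against a false claim of benefit. For complications and prematurity the costly error can be the opposite one: missing a real excess in one arm. If the closing sentence is applied as written, a sizeable difference in any of the four binary outcomes could be reported as not statistically significant, and that phrase is easily taken to mean that the arms do not differ. This matters because the abstract's Conclusions look ahead, if the trial succeeds, to use of the findings in routine primary care.

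**Working it through.** **Inputs from the protocol article.**
- Threshold: two-sided P<.001 (Statistical Analysis).
- Total sample: 280 + 231 = 511, or about 255 per arm. Allocation is about 1:1, by odd and even numbers (Randomization and Masking).
- Dropout: 30% (Sample Size Calculation), so 511 × 0.7 ≈ 358, or 179 per arm. The same section's required numbers, 210 + 178 = 388, would give 194 per arm. Results for 194 lie between the two cases below.

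**Not in the article, so assumed.** Control-arm risks of 5%, 8% and 10%, with a wider range examined afterwards, and a true doubling as the effect. The article states no power for any outcome, so there is no power figure to reproduce. Its sample size is a precision calculation (90% confidence, 5% error) that does not use .001.

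**Formula.** With p̄ = (p1 + p2)/2,

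power = Φ{ [ |p2 − p1| − z·√(2p̄(1 − p̄)/n) ] / √( [p1(1 − p1) + p2(1 − p2)]/n ) },

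where z = 3.2905 for two-sided .001 and 1.960 for two-sided .05.

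**Worked case: 8% vs 16%, n = 255.5.** p̄ = 0.12. The null SE is √(2 × 0.12 × 0.88/255.5) = 0.02875. The alternative SE is √((0.0736 + 0.1344)/255.5) = 0.02853.
- At .001: (0.08 − 3.2905 × 0.02875)/0.02853 = −0.51, power 30%.
- At .05: (0.08 − 1.960 × 0.02875)/0.02853 = 0.83, power 80%.

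**Power to declare a true doubling.**

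| Control vs intervention | 255 per arm, .001 | 255 per arm, .05 | 179 per arm, .001 | 179 per arm, .05 |
|---|---|---|---|---|
| 3% vs 6% | 5% | 37% | 3% | 28% |
| 5% vs 10% | 12% | 57% | 7% | 44% |
| 8% vs 16% | 30% | 80% | 17% | 65% |
| 10% vs 20% | 45% | 89% | 26% | 76% |
| 12% vs 24% | 60% | 94% | 37% | 84% |
| 15% vs 30% | 78% | 98% | 54% | 93% |

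Exact enumeration of the uncorrected chi-square test agrees within about 1.5 percentage points.

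**Where power for a doubling crosses 50%.**
- At .001: control risk of about 10.7% with 255 per arm, about 14.3% with 179.
- At .05: control risk of about 4.2% with 255 per arm, about 5.9% with 179.

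**What the rule does to one result.** Suppose 20/255 events against 40/255, an observed doubling.
- Pooled z-test: p̄ = 60/510 = 0.1176, z = 0.0784/0.02853 = 2.75, P about .006. The risk difference is 7.8 points, 95% CI 2.3 to 13.4.
- Unadjusted logistic regression: OR = (40 × 235)/(20 × 215) = 2.19. SE(log OR) = √(1/40 + 1/215 + 1/20 + 1/235) = 0.290, so z = 0.782/0.290 = 2.70, P about .007, 95% CI 1.24 to 3.86.

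Both intervals exclude no difference, yet the closing sentence would label the result not significant. With 20/255 in controls, 44/255 still fails (z = 3.21) and 45/255 passes (z = 3.32). The observed risk must therefore reach 17.6%, a risk ratio of 2.25.

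**Birth weight.** The article gives no SD. With an assumed SD of 400 to 600 g and a 200 g mean difference, power at .001 is 99% to 68% with 255 per arm and 93% to 45% with 179. The result for the binary outcomes does not carry over.

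**The case against.** **Scope.** The Statistical Analysis section discusses only eGWG, so its last sentence may simply restate the primary criterion and add that the test is two-sided. That reading is possible. But the primary criterion had already been set, the sentence is unrestricted, and no other standard is available for the secondary outcomes. If only eGWG was meant, the sentence needs the same edit.

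**Intervals.** A reader might infer that no interval estimate is planned for these outcomes. The article does not support that. Logistic regression yields odds ratios with intervals, and a condensed article need not say so. The defect is the stated decision rule, not a missing reporting detail.

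**Safety.** A reader might also infer that these are the trial's safety endpoints and that a null result will be presented as proof of safety. The documents do not say so. They list them as secondary outcomes, and the Introduction treats such events as hoped-for benefits, where good nutrition may "reduce the risk of adverse birth outcomes, such as preterm birth and low birth weight associated with eGWG". The intervention is nutrition messages added to routine care, and routine use is made conditional on reducing excessive weight gain. This objection stands as to framing. A two-sided rule is nonetheless as blind to a real reduction as to a real excess, so the loss of information remains.

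**Reach.** It would be too strong to say that almost any realistic excess would be missed, or that .001 alone is responsible. For control risks below about 4% (about 6% after dropout), a doubling would usually be missed at .05 as well. Above about 11% (about 14% after dropout), it would usually be detected at .001.

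**Multiplicity.** Several secondary outcomes could justify some strictness. But a Bonferroni correction for the five listed would give .05/5 = .01, ten times less strict than .001. Power at .01 with 255 per arm would be 33%, 58% and 72% for the three main cases.

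**Conclusion.** The point holds in bounded form. Read literally, the closing sentence applies two-sided P<.001 to gestational hypertension, gestational diabetes, pre-eclampsia and prematurity. For assumed control risks of 5% to 10%, power to declare a true doubling is then 12% to 45% at full recruitment and 7% to 26% after the stated dropout. At .05 it would be 57% to 89% and 44% to 76%. With full numbers the threshold is the main cause over that range. After dropout, and for rarer outcomes, sample size shares the blame.

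The conclusion rests on the literal reading of one sentence and on event rates that the article does not give. It does not extend to birth weight analysed as a mean, and it says nothing about whether .001 suits the primary comparison. The primary result is unaffected. What is at risk is the reading of the secondary outcomes.

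**What to change.** In the Statistical Analysis section:
- Limit the P<.001 criterion to the primary eGWG comparison.
- Say that each complication and perinatal outcome will be reported by arm with an effect estimate and a two-sided 95% CI: the odds ratio from the planned logistic regression or a risk difference for the binary outcomes, and a mean difference for birth weight.
- State that P≥.001 will not be read as absence of a difference or of harm.

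The cost is one or two sentences and no new data. The downside is that chance imbalances across several secondary outcomes become more visible. They must be described as estimates, not as established effects.
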